#### Confounding factors

We will include gender, age in years at time of first prescription, previous psychiatric illness/consultation, previous use of psychotropic medications such as hypnotics, antipsychotics and antidepressants, previous self-harm, measures of alcohol consumption where appropriate mean/median number of GP visits per year, body mass index, SEP (deprivation score for area or residence) and major chronic illness (including: diabetes, cancer, arthritis) using the Charlson index.^26^
^27^ Relevant Read codes will be identified either by validated code lists or by searching for each of these events in the Read code dictionaries to identify any missing Read codes. Collider bias is a potential threat to the analysis; this type of bias occurs when the association between two variables changes on conditioning of a third variable if the third variable is affected by the first two variables. Collider bias could occur if we conditioned on events that happened as a result of the prescription the patient was issued. To prevent this bias from affecting our results, we will define each covariate using data inputted prior to the first prescription.^28^ If there are missing data in the covariates we will consider using multiple imputation.

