### Inclusion and exclusion criteria

We will include patients who were older than 18 and were prescribed medicines in British National Formulary (BNF) category 4.10.2 (Nicotine Dependence) from 1 September 2006, when varenicline was introduced to the UK, to the present. We will use patients prescribed other smoking cessation products (nicotine patches, gum, lozenges, and inhalers) as controls for patients prescribed varenicline. We will include patients whose records were classified as ‘acceptable’ by the CPRD from all ‘up to standard’ general practices (GPs) at least 18 months prior to date of entry of each cohort (1st March 2005). Up to standard GPs are practices that have submitted data that meets the CPRD quality control thresholds. Patient data are defined as ‘acceptable’ by the CPRD if they meet minimum quality control standards, for example their registration period with their GP is valid.

We will exclude patients who registered at a GP less than 365 days before the first recorded prescription, to allow for high-quality assessment of baseline data and possible confounders. Patients prescribed bupropion in the year before their index prescription of varenicline or nicotine replacement therapy will be excluded from the analysis. In the primary analysis we will exclude patients initially prescribed nicotine replacement therapies and varenicline together, although in our previous analysis this only occurred for 0.25% of all prescriptions.^13^

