#### Analysis 1: Conventional cox regression

In our first analysis, a conventional observational analysis, we will estimate HRs of the outcomes using Cox-proportional hazards models and the actual prescriptions issued to the patients.^29^ Each patient's date of entry into the cohort will be the date they were first prescribed a smoking cessation therapy. The date of exit for each outcome will be the date on which they first have an event, or are censored due to end of follow-up or death or leaving the practice. We will report these associations adjusted for basic confounders (age and gender), and results adjusted for all measured covariates described above.

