#### Analysis 2: Propensity score regression

In our second analysis we will construct a sample of patients balanced on covariates and risk factors using a propensity score.^30–33^ We will construct propensity scores using a logistic regression of the actual treatment received on the covariates described above. Therefore, each participant's propensity score will be their conditional probability (odds) of receiving varenicline versus nicotine replacement therapy. We will match each patient receiving varenicline to another patient receiving nicotine replacement therapy with the closest propensity score on a ratio of 1:1 using a nearest neighbour algorithm with no replacement, and matching will be restricted to the common support region. Patients outside the common support region are those prescribed varenicline with propensity scores higher than any patient prescribed nicotine replacement therapy and vice-versa. We will estimate HRs of the outcomes using the propensity score matched sample using Cox regressions using the same entry and exit information as the conventional Cox regression analysis described above.

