#### Analysis 3: Instrumental variable analysis

In our third analysis, we will estimate the effects of smoking cessation therapies on the outcomes using physicians’ prescribing preferences as instruments for the prescriptions the GPs issue to their patients. We cannot directly measure the physicians’ preferences; therefore, we will use the prescriptions they issued to their previous patients as a proxy for their preferences. For example, if the instrument was based on just one previous prescription, physicians who previously prescribed varenicline would be categorised as a varenicline prescriber. As with our previous studies we will use seven prior prescriptions to improve the strength of the instruments.^13^
^34^
^35^ Using multiple prior prescriptions will maximise power. We will report risk differences in the outcomes using additive structural mean models estimated via the generalised method of moments.^36–38^

We will categorise each of the adverse event outcomes as occurring within 3, 6, 9, 12, 24 and 48 months of first prescription. We will do this because methods for conducting survival analysis using instrumental variables are not well developed. We will use Stata 13.1 SE to generate all results. The instrumental variable analysis will be conducted using the ivreg2 command and psmatch2 will be used to construct the propensity score.^31^
^39^
^40^ All SEs will be estimated using cluster robust SEs, which account for clustering of patients within practices.

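### Index calendar date is missing from the stated covariate list although accrual opens at varenicline's launch, leaving the analyses, above all the instrumental variable analysis, open to secular-trend confounding

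*Protocol article*

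**What the plan says.** The Confounding factors section gives a named list. It begins "We will include gender, age in years at time of first prescription, previous psychiatric illness/consultation, previous use of psychotropic medications" and ends with "body mass index, SEP (deprivation score for area or residence) and major chronic illness (including: diabetes, cancer, arthritis) using the Charlson index". Neither index date nor calendar year appears.

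Analysis 1 reuses the list: "We will report these associations adjusted for basic confounders (age and gender), and results adjusted for all measured covariates described above". Its time origin is the prescription itself: "Each patient's date of entry into the cohort will be the date they were first prescribed a smoking cessation therapy". Analysis 2 does the same: "We will construct propensity scores using a logistic regression of the actual treatment received on the covariates described above". Matching is then 1:1 on that score, with no matching on date.

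Analysis 3 cannot observe preference directly, so "we will use the prescriptions they issued to their previous patients as a proxy for their preferences". Seven prior prescriptions are used. The section names no covariates for this model, calendar or otherwise. Outcomes are binary, within windows from 3 to 48 months.

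Under Inclusion and exclusion criteria, eligible prescriptions run "from 1 September 2006, when varenicline was introduced to the UK, to the present", and nicotine replacement therapy (NRT) users from the same open window are the controls.

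**The concern.** Varenicline's share of prescriptions was zero just before accrual opened, so it must have risen. An instrument made of earlier prescriptions by the same physician follows that rise. Varenicline patients, and patients with high instrument values, will therefore tend to have later index dates. If the risk of an outcome, the way it is recorded or the kind of patient treated also changes over the years, given the listed covariates, part of the treatment contrast is a contrast between earlier and later years.

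Nothing stated absorbs this. Cox time runs from first prescription, so the baseline hazard does not carry calendar time. Age at prescription is not calendar time. Using the latest deprivation index before entry dates only the deprivation score.

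The IV analysis is most at risk for two reasons. It divides by the association between instrument and treatment, so a small link between instrument and outcome is magnified. It also uses fixed windows, and late entrants may not be observed for the whole of the longer ones. The Cox models deal with unequal follow-up by censoring; the IV description states no equivalent.

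**Working it through.** **Plan's own figures.** Power calculations gives 110 000 earlier patients and 18 000 new ones a year for 4 more years: 110 000 + 4 x 18 000 = 182 000, which matches the stated figure of around 180 000. Accrual from September 2006 to 2011 plus 4 years is about 9 years. The document states no figure for calendar-time bias, no yearly varenicline share after launch and no outcome trend. What follows is illustration under assumptions.

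**Step 1: conventional comparison.** Take 9 equal accrual years with mid-points y = 0.5 to 8.5, no drug effect, share p(y), and risk proportional to (1 - g)^y. The spurious ratio is [sum p(1-g)^y / sum p] / [sum (1-p)(1-g)^y / sum (1-p)].

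Worked case, share rising linearly from 0 to 40%, p = 0.4y/9:
- Sum of y = 40.5 and sum of y squared = 242.25.
- Mean index time, varenicline: 242.25/40.5 = 5.98 years.
- Mean index time, NRT: (40.5 - 0.4 x 242.25/9)/(9 - 1.8) = 29.73/7.2 = 4.13 years.
- The gap is 1.85 years, so the ratio is about 0.98^1.85 = 0.963 for a 2% yearly fall. The full formula also gives 0.963.

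| Assumed share | Gap (years) | Ratio, 2% fall | Ratio, 5% fall |
|---|---|---|---|
| Flat 35% | 0 | 1.00 | 1.00 |
| 0 to 20%, linear | 1.65 | 0.967 | 0.917 |
| 0 to 40%, linear | 1.85 | 0.963 | 0.907 |
| 0 to 60%, linear | 2.12 | 0.958 | 0.895 |
| To 35% in 2 years, then flat | 0.68 | 0.986 | 0.964 |
| To 40% by year 4, then down to 30% | 0.98 | 0.980 | 0.948 |

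With no outcome trend, every ratio is 1.00.

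**Step 2: IV analysis.** Let Z be the share of varenicline in seven prescriptions, X the treatment and Y the risk. The IV estimate is Cov(Z,Y)/Cov(Z,X). Simulated with no drug effect, an assumed risk of 10 per 1000 at launch, and an assumed between-prescriber SD of 0.8 or 1.5 on the logit scale. Risk differences per 1000, shown as SD 0.8 / SD 1.5:

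| Assumed share | IV, 2% fall | IV, 5% fall | Crude, 2% fall | Crude, 5% fall |
|---|---|---|---|---|
| 0 to 20% | -2.60 / -0.98 | -5.78 / -2.19 | -0.29 / -0.26 | -0.65 / -0.58 |
| 0 to 40% | -1.87 / -0.90 | -4.15 / -2.00 | -0.32 / -0.28 | -0.72 / -0.63 |
| 0 to 60% | -1.65 / -0.91 | -3.66 / -2.02 | -0.36 / -0.32 | -0.80 / -0.70 |
| 35% in 2 years, flat | -0.87 / -0.35 | -1.98 / -0.80 | -0.12 / -0.11 | -0.27 / -0.24 |
| 40%, then 30% | -1.13 / -0.52 | -2.58 / -1.18 | -0.18 / -0.16 | -0.41 / -0.36 |

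With a flat share, both estimates are zero to within simulation error. In this set-up Z and X have the same mean in each year and Y depends only on year, so Cov(Z,Y) = Cov(X,Y) and the magnification is Var(X)/Cov(Z,X). Examples are 2.60/0.29 = 9.0 and 0.91/0.32 = 2.8, so roughly 3 to 9 times. Within a calendar year Y is constant, so conditioning on year removes the bias by construction.

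**Step 3: fixed windows.** If data extraction coincides with the end of accrual (an assumption), patients entering in the last 4 years cannot complete 48 months: 72 000/182 000 = 40% of the sample. For 24 months the figure is 36 000/182 000 = 20%. These are also the patients likely to have higher instrument values. Step 2 does not include this mechanism.

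**The case against.** A reader might infer that all three analyses are confounded. The document does not support that. Bias needs both a moving share and a trend in risk, recording or case mix, given the listed covariates. The launch date implies only the first, and gives no later uptake curve. The 2009 boxed warning is a US action, with no documented effect on UK prescribing. The remark that practices are paid to record smoking status says recording is robust, not that it changed. For Analyses 1 and 2, unequal follow-up is handled by censoring. This objection stands and fixes the wording at "open to".

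It can also be said that the covariates of Analysis 3 are unstated rather than shown to exclude date, and that the full approved protocol is not at hand. That is fair for Analysis 3. It does not reach Analyses 1 and 2, where a named list is fixed and reused by reference.

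Whether the instrument starts with no varenicline at all depends on whether pre-launch prescriptions count towards the seven, which is not stated. The general upward movement does not depend on this.

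A reader might further infer that agreement among the three methods would be worthless. The figures point the other way: a trend that biases the IV estimate several times more than the crude one would tend to pull the methods apart, and planned triangulation could show that. Nor should the illustrated bias be set against the projected precision of the IV mortality result, because the baseline risk used here is assumed and not taken from the document.

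**Conclusion.** The point holds as a gap in the stated adjustment set. Index date is absent from the list used in Analyses 1 and 2, and no calendar term is named for Analysis 3, while the design ties treatment and instrument to calendar time. Confounding is possible, not demonstrated.

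Its size is unknown. Under the assumptions above (9 equal accrual years, 10 per 1000 at launch, a 2% to 5% yearly fall), the spurious IV risk difference is about -0.4 to -5.8 per 1000 and the crude one about -0.1 to -0.8. Prescriber spread alone changes the IV figure by up to 2.60/0.98 = 2.7 times. A rising outcome trend would reverse the sign, and without either trend the bias is nil. For the conventional analyses the illustrated ratio is between about 0.90 and 0.99. Incomplete 24- and 48-month windows could add to the IV bias if late entrants are kept in. This is a worthwhile low-cost improvement, held with moderate confidence, and not a flaw that invalidates the plan.

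**What to change.** Add the calendar period of the index prescription to the Confounding factors list: year, with finer intervals in the early years, or a spline of index date. Then:
- Cox models: include it as a covariate or stratum.
- Propensity score: include it in the logistic model and match within calendar period where feasible.
- IV model: include index-period indicators as exogenous covariates, and report instrument balance by period.
- Fixed windows: state how patients without a complete 24- or 48-month window are handled in the IV analysis.

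No new data are needed, since the index date defines cohort entry. The costs are slightly lower first-stage strength, because the calendar part of the instrument is removed, and possibly a few lost matches.

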##### Outcome 2: Frequency of GP and hospital attendance

We will define service use as the number of visits to GP and hospitals in the 3, 6, 9, 12, 24 and 48 months after first prescription. We will define GP appointments using the clinical data file of the CPRD. This includes all the diagnoses and symptoms that GPs record about all of their patients. As with the other outcomes, the vast majority of diagnoses and symptoms include the date on which the data were added to the database. We will use these dates to calculate the number of times each patient attends primary care. We will define the hospital visits outcome using the linked HES data. We will investigate all-cause hospitalisation and three specific causes of hospitalisation: (1) diseases of respiratory system (ICD-10=J00-J99), (2) cardiovascular disease (ICD-10=I00-I52) and (3) anxiety and depression (ICD-10=F31.3, F31.4, F31.5, F32, F40-F48). Causes of hospitalisation are available for approximately half of the sample. Again these data contain the date on which the event occurred, which we will use to define attendance to secondary care within 3, 6, 9, 12, 24 and 48 months after first prescription.

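### Pregnancy at the index prescription is neither an exclusion nor a covariate, so the Cox and matched estimates for all-cause hospitalisation and GP attendance are open to confounding if the two products are used unequally in pregnancy

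*Protocol article*

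**What the plan says.** Inclusion and exclusion criteria (Protocol article): "We will include patients who were older than 18 and were prescribed medicines in British National Formulary (BNF) category 4.10.2", from 1 September 2006. Three patient-level exclusions concern prior care or treatment. They are short registration ("We will exclude patients who registered at a GP less than 365 days before the first recorded prescription"), recent bupropion ("Patients prescribed bupropion in the year before their index prescription of varenicline or nicotine replacement therapy will be excluded from the analysis") and, in the primary analysis, dual prescribing ("we will exclude patients initially prescribed nicotine replacement therapies and varenicline together"). None concerns pregnancy.

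Confounding factors: the list opens "We will include gender, age in years at time of first prescription, previous psychiatric illness/consultation". It continues through psychotropic drugs, self-harm, alcohol, GP visits, body mass index and deprivation, and ends with "major chronic illness (including: diabetes, cancer, arthritis) using the Charlson index". Pregnancy is not on it. The section also requires every covariate to be defined from data entered before the first prescription.

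Analyses 1 and 2: the fully adjusted Cox model and the logistic model for the propensity score both use this list.

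Outcome 2: "We will investigate all-cause hospitalisation and three specific causes of hospitalisation". GP attendance is counted from dated entries in the clinical file. Neither measure sets maternity care aside. The word pregnancy and related terms appear nowhere in the article.

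**The concern.** Pregnancy at index nearly guarantees a hospital admission within about nine months and brings a run of GP contacts, for reasons unrelated to the smoking cessation product. Few omitted variables predict all-cause admission so strongly. If pregnancy also affects which product is chosen, it is a confounder that the Cox and matched analyses cannot see. Part of any difference in admissions or GP visits would then be maternity care.

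The article relies on triangulating three methods. The instrument is the physician's previous prescribing, which does not depend on measuring each patient-level confounder. An avoidable confounder in the other two methods could therefore make the three disagree for a reason that has nothing to do with their different assumptions.

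**Working it through.** **Textual check.** The three places that could deal with pregnancy are the entry rules, the covariate list and the outcome definitions. The entry rules are silent, the covariate list is silent, and Outcome 2 is unrestricted. As written, maternity admissions and antenatal contacts are events, and neither the Cox model nor the propensity score can account for them.

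**Sample size.** The article gives no figure on pregnancy. Its expected sample reproduces: 110 000 + 4 × 18 000 = 182 000, stated as around 180 000. Outcome 2 says that causes of hospitalisation are available for about half the sample. I take 180 000 / 2 = 90 000 as the linked sample.

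**Assumed inputs (none is in the article).** No drug effect; 9-month admission risk 0.12 if not pregnant and 0.95 if pregnant; a share p of NRT patients pregnant at index; no pregnant women on varenicline (upper bound); 25% to 35% of patients on varenicline.

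**Formulas.**
- Varenicline risk = 0.12
- NRT risk = 0.12(1 - p) + 0.95p
- False risk difference = 0.12 - NRT risk = -0.83p
- False HR = ln(1 - 0.12) / ln(1 - NRT risk), a summary from the 9-month risks
- SE(log HR) = sqrt(1/E_v + 1/E_n), where E is expected events per arm, ignoring clustering by practice

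| p | NRT risk | Difference per 1000 | HR | \|z\| |
|---|---|---|---|---|
| 0.5% | 0.12415 | -4.2 | 0.964 | 1.6 to 1.8 |
| 1% | 0.1283 | -8.3 | 0.931 | 3.2 to 3.6 |
| 2% | 0.1366 | -16.6 | 0.870 | 6.3 to 7.0 |

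**Partial imbalance.** If the varenicline share is half the NRT share, 1% on NRT gives 0.12415 - 0.1283 = -4.2 per 1000 (HR 0.965). With 2% on NRT it is 0.1283 - 0.1366 = -8.3 per 1000 (HR 0.935).

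**Equal shares.** The two risks are identical and the bias is 0. Only precision is affected.

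**Other base risks.** With p = 1% and complete separation, a base risk of 10% gives -8.5 per 1000 (risk ratio 0.92), and 20% gives -7.5 per 1000 (risk ratio 0.96). The ratio moves towards 1 as the base risk rises, as it will in the 24- and 48-month windows.

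**Does adjusting for age and gender deal with it?** Let stratum s hold a fraction w_s of NRT patients, with a share p_s pregnant. Within the stratum the false difference is -0.83p_s. Standardised to the NRT patients, the total is -0.83 × sum(w_s p_s) = -0.83p, the same as the crude figure. This takes a constant base risk and the upper-bound case. Age and gender remove imbalance that comes from a different age-sex mix, but not imbalance that arises because pregnancy itself influences the choice of product.

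**The case against.** The strongest objection is that confounding needs unequal use of the products in pregnancy, and nothing in the article says this happens. The safety concerns it describes for varenicline are neuropsychiatric and cardiovascular. That stands: the bias is conditional, and its range includes zero.

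The figures are also an upper bound. They assume complete separation, one outcome and one window, with invented base risk, pregnancy share and varenicline share. Even under separation, 0.5% gives |z| below 2, and allowing for clustering by practice could lower the z-values. This stands too.

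The article admits unobserved confounding in general and plans an instrumental variable analysis aimed at it. That limits the reach of the point, but the other two methods are still reported, and pregnancy is something that GP records can hold.

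The article is a condensed account, and a separate approved ISAC protocol exists. However, the article sets out explicit criteria, covariates and outcome definitions, and the point is about those as stated. If the full protocol already handles pregnancy, only the article's account needs correcting.

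A reader might go further and infer that postnatal depression is being counted, or that depression and abstinence are biased in the same direction as admissions. The document does not support either. The hospital codes for anxiety and depression are F31.3, F31.4, F31.5, F32 and F40-F48, with no puerperal code, and the primary care Read code lists are not shown. For abstinence no direction can be claimed. More quitting in pregnancy and more frequent recording of smoking status would push the result opposite ways.

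**Conclusion.** The point holds in a limited form. Pregnancy at index is missing from both the exclusions and the covariates, while two outcomes count maternity care. The consequence is possible confounding of the Cox and matched estimates for all-cause hospitalisation and GP attendance.

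Under the stated assumptions the false difference in 9-month admissions is at most about -4 to -17 per 1000 (HR 0.96 to 0.87) for 0.5% to 2% pregnant among NRT patients. It is about half that if varenicline has half the NRT share, and zero if the shares are equal. No size has been worked out for GP attendance. The instrumental variable analysis is less affected if its own assumptions hold.

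It would be wrong to conclude that the plan will produce a spurious drug effect. The document does not show that pregnancy differs between the products. Nor should the point be extended to depression or abstinence, where no effect is established.

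**What to change.** Choose one of two changes:

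- In Inclusion and exclusion criteria, exclude from the analysis cohort women with a recorded pregnancy that is current at the index date; or
- In Confounding factors, add that indicator, so that it enters both the Cox model and the propensity score.

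Either way, define pregnancy only from data entered before the first prescription, as the Confounding factors section already requires. Delivery records after index should not be used to infer it. Tabulating the indicator by product would show whether use is in fact unequal.

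Keep all-cause hospitalisation as defined, because all-cause use of services is a stated aim and obstetric admissions also include pregnancies that begin after index. A version without obstetric admissions belongs only in a sensitivity analysis.

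The cost is one more code list and, with the exclusion, a small loss of sample. Recording of pregnancy in GP data will be incomplete, so some residual confounding could remain.
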